## Abstract

**Background:**

Household decision-makers decide about service use based largely on the costs and perceived benefits of health interventions. Very often this leads to different decisions than those imagined by health planners, resulting in under-utilisation of public services like immunisation. In the case of Lasbela district in the south of Pakistan, only one in every ten children is immunised despite free immunisation offers by government health services.

**Methods/design:**

In 32 communities representative of Lasbela district, 3344 households participated in a baseline survey on early child health. In the 18 randomly selected intervention communities, we will stimulate discussions on the household cost-benefit equation, as measured in the baseline. The reference (control) communities will also participate in the three annual follow-up surveys, feedback of the general survey results and the usual health promotion activities relating to immunisation, but without focussed discussion on the household cost-benefit equations.

**Discussion:**

This project proposes knowledge translation as a two-way communication that can be augmented by local and international evidence. We will document cultural and contextual barriers to immunisation in the context of household cost-benefit equations. The project makes this information accessible to health managers, and reciprocally, makes information on immunisation effects and side effects available to communities. We will measure the impact of this two-way knowledge translation on immunisation uptake.

## Background

Despite billions of dollars spent on childhood immunisation, some countries have never reached universal childhood immunisation (UCI), and many more have been unable to sustain it. An estimated 1.5 million deaths under 5 years of age can be prevented by vaccination each year, measles making up 37% *H. influenzae* b-related disease 30%, and pertussis 19%[1]. In many countries, there is dramatic underutilisation of the offer of free immunisation. One reason for this is a difference between understanding of the costs and benefits of vaccination in international public health circles, and what primary decision-makers for children know about immunisation and its costs.

There is a gap between the way public health specialists understand immunisation benefits, and the cost-benefit equations that household decision-makers apply to their children's immunisation. In settings like Pakistan, where an expanded program of immunisation is offered free of charge, uptake is largely determined by access to services and the attendant cost-benefit assessments by parents and caregivers. These assessments could be influenced by access to knowledge and conditioned by gender and social inequalities.

Although communication of risks and benefits by service providers can influence health-seeking behaviour [2], current approaches to health communication do not always achieve the expected results. Efforts frequently produce an increase in knowledge without a corresponding change in attitudes or behaviour[3]. This is at least partly because conventional risk communication presumes to inform an uninformed public and to reduce irrational thinking. Questioning the value of these conventional one-way knowledge transfer (KT) initiatives, more holistic perspectives take account of social and cultural influences[4]. Impact studies of communication strategies to increase vaccination in the USA, Russia and Mozambique all highlight the need of multi-channel targeting of multiple groups – families, communities, health practitioners and opinion makers, such as community and religious leaders[5-7].

Current devolution reforms in Pakistan are expected to make service delivery more effective and to support institutionalised participation of community members[8,9]. Service delivery is now a district function, yet the provinces are still responsible for planning and monitoring health services [9]. The expanded programme of immunisation (EPI) remains a federal responsibility. The 2002 Pakistan Integrated Household Survey claimed an increase in immunisation coverage, mostly in the urban areas. The proportion of fully immunised children aged 12–23 months rose from 49% to 53%, and even this small gain was not consistent countrywide. In Balochistan, where the project will be located, immunisation coverage fell from 34% in 1998–9 to 24% in 2000–1, mostly attributed to diversion of resources to the polio eradication campaigns[10].

Balochistan is Pakistan's largest province (347,000 km^2^) and has the lowest population density (6.5 million, 19/km^2^). It covers more than 40% of the land area, but has less than 5% of the national population. The disease burden in Pakistan is still largely poverty-related, much of it preventable by immunisation[11,12].

Lasbella, in the south of Balochistan is one of the province's poorest districts. In 2003 there were around 50,000 women of childbearing age in this district. There were 11,594 infants under the age of one year, and reflecting the very high infant mortality, 8,140 children aged 12–23 months. The new district administration employs 39 full time vaccinators, but still only achieves symbolic coverage. The problem does not appear to be one of supervision or management. The vaccinators report to a superintendent, who in turn reports to the Deputy District Health Officer, who reports to the Executive District Officer for Health.

## Statement of the research issue and approach

We believe that health care consumers make rational decisions from a cost-benefit perspective[13,14]. Based on their own knowledge, mothers and guardians weigh up the costs and the benefits of immunisation: how much time will it take, how much will it cost, will it work, will there be side effects and what will happen if I do not go. We propose that immunisation uptake is largely determined by this cost-benefit equation.

But the rationality of such decisions is a "bounded rationality" [15]. This concept enables health planners to see such factors as social norms and attitudes not as obstacles to rationality but rather mechanisms that facilitate fast and accurate decisions, and more efficient learning. In addition, the weigh-up of risks may be sharply discounted between the time of the immunization and the time of possible infection. Also, gender and poverty probably affect the household cost-benefit equation. The poor, who typically have less access to services and less information about services, almost certainly weigh up the costs and benefits in a different way than do the rich [16]. Diseases like measles and pertussis may be an inconvenience for the well-nourished, whereas for the malnourished, they can be a question of life or death. Costs of *not *vaccinating (disease burden, care and funerals) are borne disproportionately by the poor; in a single epidemic, these diseases can destroy a household economy[17].

### The household cost-benefit equation is, therefore, a lens through which to view immunisation and the obstacles to immunisation

A focus on these equations gives value to the way ordinary people see immunisation, allowing their views to be taken systematically into account. It gives primacy to household decisions, and recognises that communication about immunisation is a two-way street. We propose to test the importance of this household cost-benefit equation that decision-makers for children derive from their knowledge, attitudes, social norms, intentions, sense of agency and degree of socialisation about immunisation.

The hypothesis is that this dynamic equation can be influenced by two-way knowledge translation (KT), and based on this culture-appropriate exchange, that people will adjust their household cost-benefit equations and their uptake of immunisation. A corollary of the household cost-benefit equation is accessible to planners and health service managers: cost-gains. Derived from the same data used by communities for their cost-benefit equations, cost-gains offers a common language for interaction between health services and communities. If local health managers understand how primary decision makers assess immunisation – their cost-benefit equations – this can improve their engagement with communities and lead, in turn, to sustainable UCI.

## Methods

### Objective 1. Identify the *barriers and information imbalances *that reduce childhood immunisation, in particular increasing understanding of the household cost-benefit equations underlying uptake of immunisation

Randomised controlled cluster trials are fairly widely used in developed countries, and have been introduced in several developing countries[18-20].

#### Randomisation

From the latest Pakistan census, 32 enumeration areas were randomly selected to represent the population of Lasbela district. Once the baseline survey was completed, clusters were randomised into intervention and control, with precautions about the usual biases of this design[21]. In each cluster, interviewers contacted homes of 100 children under the age of 24 months of age (a total of 3344 households). Three successive cycles that examine successive cohorts of children in this age group, and the same number of households in each site (not necessarily the same households) will preserve the proportional representation.

#### Design of survey instruments

Questionnaires were adapted from international EPI standards. Additional fact-finding tools will produce qualitative evidence – key informant interviews, service worker questionnaires, protocols for institutional reviews and focus group discussions. The results of each round might identify additional stakeholder-driven issues and priorities and be used to refocus the subsequent survey cycles.

#### Survey content

In addition to baseline data about the coverage with and obstacles to immunisation, we enriched the standard KAP approach[22] with a behaviour change model adapted by CIET to measure youth responses to risk. The beyond-KAP approach, "cascada", refers to **c**onscious knowledge about immunisation and its side effects, **a**ttitudes to childhood immunisation, **s**ocial norms (what neighbours do) and positive or negative deviation from those norms, intentions to **c**hange or to vaccinate in the future, **a**gency (expectancy of self-efficacy or collective efficacy) and **d**iscussion about immunisation, its benefits and side effects. The outcome of this "cascada" is the **a**ction, immunisation. We will document perceived and real costs of immunisation and non-immunisation, and the household weigh up of costs and benefits.

#### Piloting

Eight rounds of piloting in non-sample sites included testing new sections of the instrument, testing the instrument for flow, and then testing the instrument as a whole in order to finalise the process. The pilot exercises assisted in refining the instruments, testing for clarity and ensuring proper translation.

#### Ethical review

Two review panels, one at the University of Ottawa and a panel in the south of Pakistan registered with the US Government's Office of Human Research Protections, deliberated the ethical issues and approved the study.

### Objective 2. Formulate and implement knowledge transfer based on household cost-benefit equations, compared with health information in reference (control) communities

#### Intervention

We will update and translate available knowledge on immunisation and combine this with data from the baseline as an intervention focussed on the household cost-benefit equation. Mass media channels can increase awareness and knowledge, but interpersonal channels seem to work better in changing attitudes and behaviour[23,24]. A combination of communication channels could, therefore, include mass media appeals, reminder systems and engagement through trusted sources, and addressing risks and benefits of vaccination in an understandable manner[25-28]. Upon consideration of the evidence, people will hopefully adjust their household cost-benefit equations. We will measure this adjustment in the subsequent cycles.

#### Analysis

We will estimate the impact of this knowledge transfer on changing beliefs and practices of decision-makers for children and, as a consequence, immunisation uptake. Differences between intervention and reference sites will be analysed for independence from age, sex, household employment, community size, remoteness and other factors. Risk analysis will rely on the Mantel-Haenszel procedure and contrasts reported as the odds ratio (OR) or risk difference (RD)[29-31]. In the analysis, each site or cluster is treated as a mini-universe characterised by certain social dynamics, history, culture and collective practices. Because qualitative data are coterminous (they coincide with the same population) with the individual questionnaires it is easy to link quantitative and qualitative data[32]. An unconditional logistic regression model will be developed where appropriate, using a step-down approach from a saturated model[33].

We also seek to express a planning-appropriate perspective that fits the household cost-benefit perspective. 'Gain' is the theoretical proportion of the *entire *population that stands to benefit from the removal of an obstacle or the universalisation of an intervention. It is calculated by multiplying the risk difference (risk among exposed minus risk among unexposed) by the proportion requiring intervention (those exposed, if the interest is to remove risk factors).

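### The analysis does not commit to adjusting the 18 versus 14 comparison for each community's baseline uptake, although this was measured before randomisation

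*Protocol article*

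**What the plan says.** All references are to the protocol article.

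- **Baseline.** The Abstract (Methods/design) reports that "3344 households participated in a baseline survey on early child health". The Survey content section shows that uptake was part of it: "In addition to baseline data about the coverage with and obstacles to immunisation".
- **Allocation.** The Randomisation section says: "Once the baseline survey was completed, clusters were randomised into intervention and control, with precautions about the usual biases of this design". It does not say what the precautions are, and it describes no matching or stratification on uptake. The Abstract gives the number of intervention communities: "In the 18 randomly selected intervention communities, we will stimulate discussions on the household cost-benefit equation, as measured in the baseline".
- **Adjustment.** Under Objective 2, Analysis: "Differences between intervention and reference sites will be analysed for independence from age, sex, household employment, community size, remoteness and other factors". The same section relies on Mantel-Haenszel contrasts (odds ratio or risk difference). Where appropriate it adds an unconditional logistic model, reduced step by step from a saturated one.
- **Follow-up.** The survey is repeated yearly for three years in both arms. Each round takes a new cohort of children under 24 months and need not return to the same households. The Repeat survey, Objective 4 and Discussion sections expect to see trends over time, but none of them ties a trend to the between-arm estimate.

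**The concern.** A community's own earlier coverage is usually among the best predictors of its later coverage. The Analysis section itself treats each cluster as having its own history and collective practices, which implies differences that persist. Because each round may sample different households and a new cohort of children, no child-level baseline exists. The community's baseline proportion is the only baseline value of the outcome available.

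The article goes as far as naming adjusters and leaves this one out. The open end of the list does not settle the matter. Combined with step-down selection, it allows baseline uptake to be left out, entered or dropped once the follow-up data are in view.

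Two things are at stake with only 32 units. Precision that the trial has already paid for may not be used. And if the realised allocation is uneven at baseline, part of that gap carries into the unadjusted follow-up difference, where it can look like an effect or hide one.

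**Working it through.** The article gives no ICC, correlation over time, effect size or power, so there is no design figure to reproduce. What follows is an illustration over a range of assumptions, on the risk-difference scale and for one follow-up round against baseline.

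**Inputs from the article**
- Communities: 32 (Randomisation: "32 enumeration areas were randomly selected to represent the population of Lasbela district"), of which 18 intervention; 32 − 18 = 14 control.
- Children per community: m = 3344 / 32 = 104.5, taking one child per household. The Randomisation section also speaks of 100 per cluster (32 × 100 = 3200, 4.3% lower), which makes no material difference here.
- Coverage: p = 0.10, from the Abstract (Background): "only one in every ten children is immunised despite free immunisation offers by government health services".

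**Assumed**
- ICC of 0.02, 0.05, 0.10 or 0.20.
- Correlation over time of true community coverage, c = 0.5 or 0.8.
- Same variance at baseline and follow-up.

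**Step 1. Chance difference between arms**

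Design effect: DE = 1 + (m − 1) × ICC = 1 + 103.5 × ICC.

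SE = √[ p(1 − p)/m × DE × (1/18 + 1/14) ]

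Without clustering: √[ 0.09/104.5 × 0.12698 ] = 0.01046, or 1.046 points. Hence SE = 1.046 × √DE. At ICC 0.05, DE = 6.18 and SE = 1.046 × 2.485 = 2.60 points. The same SE applies to the baseline difference and to an unadjusted follow-up difference.

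**Step 2. Gain from adjustment**

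Reliability of a community's measured baseline: R = m × ICC / DE. At ICC 0.05, R = 5.225 / 6.175 = 0.85.

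Correlation of measured baseline with measured follow-up: r = c × R. Variance after covariate adjustment, relative to none: 1 − r². At ICC 0.05 and c = 0.5, r = 0.42 and 1 − r² = 0.82. At c = 0.8, r = 0.68 and 1 − r² = 0.54.

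| ICC | DE | SE (points) | 95% range of chance baseline difference | Chance of a gap above 5 points | Variance factor, c = 0.5 | Variance factor, c = 0.8 |
|---|---|---|---|---|---|---|
| 0.02 | 3.07 | 1.8 | ±3.6 | 0.6% | 0.88 | 0.70 |
| 0.05 | 6.18 | 2.6 | ±5.1 | 5% | 0.82 | 0.54 |
| 0.10 | 11.35 | 3.5 | ±6.9 | 16% | 0.79 | 0.46 |
| 0.20 | 21.70 | 4.9 | ±9.5 | 31% | 0.77 | 0.41 |

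The variance reduction is therefore 12–23% at c = 0.5 and 30–59% at c = 0.8. At c = 0.8 the SE falls from 1.8 / 2.6 / 3.5 / 4.9 to 1.5 / 1.9 / 2.4 / 3.1 points.

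**Step 3. What this means at ICC 0.05**

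The approximate detectable difference (80% power, two-sided 5%, t quantiles on 30 df unadjusted and 29 df adjusted) falls from 7.5 points to 6.8 at c = 0.5, or to 5.5 at c = 0.8.

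Given a measured baseline gap of 5 points, the unadjusted follow-up difference is expected to be off by r × 5: 0.42 × 5 = 2.1 points at c = 0.5, or 0.68 × 5 = 3.4 points at c = 0.8.

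The ranges use a normal approximation, which is roughest at ICC 0.20. The variance factors ignore the small cost of estimating the slope from 32 communities.

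**The case against.** The strongest objection is that this is an omission in a condensed article. The covariates of the main model are commonly left to an analysis plan, and a fuller plan may exist. That lowers confidence but does not remove the point: the article does state adjusters, and it couples an open list with data-driven selection. The recommendation is to commit, not to correct a false statement.

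Several stronger readings are tempting, and the documents do not support them.

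- *A reader might infer that baseline uptake is excluded, so that any imbalance must remain in the estimate.* The list ends with an unspecified group of further factors, so baseline uptake is left open rather than ruled out.
- *A reader might infer that the estimate is biased.* After randomisation, chance imbalance adds variance and a conditional error in the realised allocation. It does not bias the estimator, and a standard error that respects the clustering already reflects that variance.
- *A reader might infer that nothing guards the allocation.* The Randomisation section does mention precautions. They are unspecified, so they neither establish balance on uptake nor allow one to say that no protection exists.
- *A reader might infer that a large gap is likely.* That depends on the ICC: a gap above 5 points has probability 0.6% at ICC 0.02 and 31% at ICC 0.20.
- *A reader might infer that the listed adjusters carry none of this information.* Remoteness and community size may carry part of it, and then the extra gain from baseline uptake would be smaller than shown.

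It is also fair to say that the planned tracking of trends would probably make a baseline gap visible. Seeing a gap is not the same as having a prespecified rule for handling it in the arm comparison.

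**Conclusion.** The point holds as a lack of commitment. Uptake was measured in every community before randomisation, and the Analysis section does not undertake to use it in the 18 versus 14 comparison. What is lost is precision, together with protection against conditional error and against a choice of covariates made after the data are seen.

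The size depends on two quantities the article does not give. It runs from a modest 12% of the variance (ICC 0.02, correlation 0.5) to 59% (ICC 0.20, correlation 0.8). The lower end is a real possibility, since each round samples a new cohort of young children and district-wide capacity work runs alongside. Even there adjustment is worth having, because the data are already in hand. The change is advisable; its absence does not invalidate the trial.

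**What to change.** In the Analysis section, prespecify each community's baseline uptake as a covariate in the between-arm analysis and state that it is exempt from step-down deletion. Two forms would serve:

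- a cluster-level ANCOVA of follow-up coverage on arm and baseline coverage, across the 32 communities; or
- a regression on children that accounts for clustering, with the community's baseline proportion as a covariate.

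Treat each cascada outcome in the same way, with its own baseline community mean. The covariate has to be at community level, because the children differ between rounds.

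Plain change from baseline is not a good substitute. Its variance factor is 2(1 − r), which at ICC 0.05 and correlation 0.5 is 2 × (1 − 0.423) = 1.15, worse than no adjustment. The ANCOVA factor 1 − r² = (1 − r)(1 + r) never exceeds it.

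Cost: no new data and one degree of freedom of about 30. The section names only Mantel-Haenszel contrasts and unconditional logistic regression, so either form means a little more analysis work than adding a word to the list. The commitment is worth most if dated before any follow-up data are analysed by arm.

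### Communities are randomised, but the methods named for comparing the arms do not, in standard form, allow for correlation within communities

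*Protocol article*

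**What the plan says.** The unit of randomisation is clear. Under Randomisation, "32 enumeration areas were randomly selected to represent the population of Lasbela district", and after the baseline survey "clusters were randomised into intervention and control". The abstract (Methods/design) gives 18 intervention communities, which leaves 14 controls. Within each cluster, "interviewers contacted homes of 100 children under the age of 24 months of age (a total of 3344 households").

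The Analysis section under Objective 2 first says that differences between intervention and reference sites will be examined for independence from age, sex, household employment, community size, remoteness and other factors. It then names the methods: "Risk analysis will rely on the Mantel-Haenszel procedure and contrasts reported as the odds ratio (OR) or risk difference (RD"), and later "An unconditional logistic regression model will be developed where appropriate", reduced step by step from a saturated model.

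Two sentences touch on clusters. In Analysis, "each site or cluster is treated as a mini-universe characterised by certain social dynamics, history, culture and collective practices". In Randomisation, the allocation was made "Once the baseline survey was completed, clusters were randomised into intervention and control, with precautions about the usual biases of this design". The article mentions no cluster-level test, robust variance, random effect, GEE, ICC or design effect.

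**The concern.** When whole communities are allocated, the evidence on the intervention comes from differences between 18 and 14 communities, not from some 3,300 independent children. Mantel-Haenszel and ordinary logistic regression, in the form in which they are usually run, take each child as an independent observation. The Analysis section itself gives a reason to doubt that: it describes each site as sharing its own social dynamics, history, culture and collective practices, which is what makes children in one site alike in uptake.

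At stake is the study's main question, whether the knowledge translation raises immunisation uptake. If the variance leaves out the between-community part, an ordinary chance difference between two groups of communities can readily pass as an effect. The article intends the result to carry weight: under Objective 4 it hopes to support a change in how resources are allocated.

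**Working it through.** The article states no sample-size calculation, alpha, ICC or interval width, so there is no figure of its own to reproduce. The check works out what follows if the named methods are applied to individual children.

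**Inputs from the article.** 32 clusters, 18 intervention (abstract and Randomisation). Controls: 32 − 18 = 14. Households: 3344, so the mean cluster size is m = 3344/32 = 104.5. Children per arm, taking one per household: 18 × 104.5 = 1881 and 14 × 104.5 = 1463. Uptake is about 10% (abstract, one child in ten).

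**Assumptions.** ICC from 0.005 to 0.10, nominal two-sided 5% level, equal cluster sizes, and the child as unit of analysis.

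**Formulas.**
- Design effect: DEFF = 1 + (m − 1) × ICC = 1 + 103.5 × ICC.
- Factor by which the naive standard error is too small: √DEFF.
- True type I error of a nominal 5% test: 2 × [1 − Φ(1.96/√DEFF)].

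| Assumed ICC | DEFF | √DEFF | True type I error | Effective sample (3344/DEFF) |
|---|---|---|---|---|
| 0.005 | 1.52 | 1.23 | 11% | 2204 |
| 0.01 | 2.04 | 1.43 | 17% | 1643 |
| 0.02 | 3.07 | 1.75 | 26% | 1089 |
| 0.05 | 6.18 | 2.48 | 43% | 542 |
| 0.10 | 11.35 | 3.37 | 56% | 295 |

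**Simulation.** 20,000 beta-binomial trials per setting, 18 against 14 clusters of 105 and no true effect, agreed within one percentage point. At 10% uptake a pooled child-level test rejected in 11.0%, 17.1%, 25.9%, 43.0% and 56.7% of trials. A t-test on the 32 community proportions stayed between 4.6% and 5.4% at every ICC tried, at 10% uptake and at 24% (the provincial figure in Background).

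**Interval width for the risk difference at 10% uptake.** Naive SE = √[0.10 × 0.90 × (1/1881 + 1/1463)] = 1.05 percentage points, so the naive 95% half-width is 1.96 × 1.046 ≈ 2.05 points. With clustering and 30 degrees of freedom (t = 2.042) it is 2.042 × 1.046 × √DEFF: about 3.0 points at ICC 0.01, 5.3 at 0.05 and 7.2 at 0.10. The naive 95% interval would then cover the true value about 83%, 57% and 44% of the time.

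**Would stratifying by site repair it?** In site i, let a and b be immunised and non-immunised children under intervention, c and d the same under control, and n the total. The Mantel-Haenszel OR is Σ(ad/n) / Σ(bc/n). In an intervention site c = d = 0, and in a control site a = b = 0, so every term is zero and the OR is 0/0. The weights for the risk difference, (a + b)(c + d)/n, are zero as well. Site indicators in the logistic model fail for the same reason: arm is fully determined by site.

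**The case against.** The best defence is that the article names an estimator, effect measures and a model family but gives no variance formula, test or interval. A condensed article may leave that to the full plan, and Mantel-Haenszel or logistic regression with a cluster-adjusted variance would be valid. The word unconditional separates the model from conditional (matched) logistic regression and does not exclude robust errors. This shows that the named methods can be rescued. It does not remove the point: the article fixes its methods, an adjusted variance appears nowhere in it, and the methods followed as written do not match the unit of randomisation.

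A reader might infer that the plan ignores clustering altogether. The text does not support that. It describes each site as a universe of its own and mentions precautions at randomisation, so clusters were in mind. But the first sentence leads into linking qualitative and quantitative data, the second concerns biases of the design, and neither says how the standard error is obtained. The method references cannot be seen here, so an adjustment in them can be neither credited nor ruled out.

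Three further reservations stand. The child as unit of analysis is inferred from the individual questionnaires and child-level covariates; no sentence states it. Risk analysis may also cover obstacles to immunisation, which vary within communities, and there stratifying by site works. Still, the sentence directly follows the comparison of intervention and reference sites, so it plausibly covers the trial contrast too. And the article designates no analysis as confirmatory. Adjusting for community size and remoteness may lower the residual ICC but does not correct the variance.

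**Conclusion.** The point holds for the methods named for the intervention contrast. Used in standard form on individual children they understate the standard error, and stratified by site Mantel-Haenszel cannot estimate the arm effect at all.

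The size is conditional. It would go too far to say that the trial's standard errors will be 1.4 to 3.4 times too small: that range belongs to assumed ICCs of 0.01 to 0.10, and the article gives none. Nor does the article state an interval width; the half-width of about 2 points is what a naive calculation would give. The direction is not in doubt for any positive ICC, and with about 104 households per community even an ICC of 0.005 more than doubles a nominal 5% error rate.

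**What to change.** For the intervention effect on uptake, state one analysis that respects the 32 communities. Any of these would do:

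- a t-test, regression or permutation test on the 32 community values, with about 30 degrees of freedom for the unadjusted comparison;
- a mixed or GEE model with community as the cluster and a small-sample correction;
- Mantel-Haenszel or logistic regression with a cluster-adjusted variance.

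Report the risk difference or odds ratio with a cluster-based 95% confidence interval. If survey rounds are combined, the analysis should also reflect that the same communities return each year. Say explicitly that stratification by site is reserved for exposures that vary within a site.

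The cost is a reworded Analysis section, a little more programming and wider confidence intervals. No further data are needed. It should be settled before the follow-up surveys are analysed.
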